### Health economic analysis

The health economic analysis will comprised two parts, both of which will assess the cost-effectiveness of health coaching with a web-based IT platform (IGR3) compared with health coaching alone (IGR2) among people with prediabetes. The first will be an incremental cost-effectiveness analysis from a clinical commissioning group perspective using patient satisfaction and intervention costs to derive a cost per additional unit of patient satisfaction. The second analysis will be conducted from an NHS and personal social services perspective [44]. Costs will include intervention costs and healthcare and social services resource costs. The quantity of resource use will be collected by questionnaire and a set of national average unit costs will be applied (e.g. [45]). The use of the EQ-5D-5 L will enable the estimation of quality-adjusted life years by calculating the area under the curve [46]. An incremental cost-effectiveness ratio (cost per additional quality-adjusted life year) will be used to assess cost-effectiveness of IGR3 in comparison with IGR2. Cost-effectiveness planes and cost-effectiveness acceptability curves will be constructed to reflect any uncertainty in the results and threshold.

### Qualitative study

Process evaluations of complex interventions can be used to explain outcomes through an evaluation of how casual assumptions about how an intervention might work are related to the way it was implemented and how it produces change within particular contexts. Drawing on guidance from the Medical Research Council, a focus on understanding implementation (the what and how of intervention delivery), mechanisms of impact (pathways to change), and contextual factors can inform the design and conduct of a process evaluation [47]. However, the framework proposed by the Medical Research Council is not easily operationalized in the absence of a programme theory set out as a logic model. Programme theory articulates the hypothesized connections between the programme components and the outcomes to be assessed and is often underpinned by a theory of change [48]. Logic models offer a visual way of representing the ‘if… then…’ relationships between the resources needed to deliver the programme, the activities planned and their outputs, and the intended results of the programme. Using programme theory to drive the evaluation can help differentiate between programme theory failure, i.e. whether the intervention failed because of weaknesses in the underlying theory of change, and programme implementation failure, i.e. whether the intervention failed because of weaknesses in the way it was delivered [49].

In this trial, the theory of change presupposes that health coaching supported by web-enabled self-monitoring and feedback and education will increase patient activation, which, in turn, will result in increased patient satisfaction, reductions in the cost of service delivery and positive changes in health behaviours known to delay or prevent type 2 diabetes (Fig. 4). As such, greater effects are anticipated among participants in the web plus telephone coaching group than in the telephone-only group.

**Fig. 4 Fig4:**
[figure not shown]
Theory of change model in CATFISH

At the heart of this model is the concept of patient activation, which captures key ingredients known to predict patients’ capacity to engage in self-managing their health and use of healthcare: knowledge, skill and confidence [38]. Higher patient activation has been shown to predict engagement in preventive behaviours, such as attending regular check-ups, and healthy behaviours, such as regular exercise, treatment adherence and self-monitoring [50]. Moreover, activated patients are more likely to have clinical outcomes, such as HbA1c concentration and body mass index in the normal range [51]. Critically, highly activated patients are more satisfied with their care experience and have lower rates of hospital admissions and emergency room use, possibly leading to reductions in the cost of their care [52, 53].

Taking this theory of change as a starting point, Fig. 5 shows the logic model for the web plus telephone health coaching intervention tested in this trial. It is read from left to right, and includes a detailed breakdown of the resources and activities associated with delivering the intervention, along with details of the anticipated results, which include outputs, outcomes and impact over time. This logic model will facilitate qualitative evaluation of key programme vantage points related to context, implementation and outcomes [54]. While this trial is not a formal test of clinical effectiveness, qualitative evidence drawn from patient participants and also from health professionals engaged in delivery of the interventions will strengthen our understanding about user experience and impact of what was delivered, leading to greater opportunities to report about how the interventions might work in comparable and different contexts. Specific to the evaluation of IGR3, the evaluation will also be informed by evidence about dynamic factors that moderate individual acceptance of IT [55].

**Fig. 5 Fig5:**
[figure not shown]
Logic model of programme components in CATFISH. DNS, domain name system

#### Qualitative data collection

Qualitative assessments using semi-structured interviews with patient participants drawn from both arms of the trial will take place after quantitative follow-up data have been collected. Semi-structured interviews offer opportunities to cover, in-depth, a range of topics relevant to the research questions, but also allow for exploration and probing of issues raised during the interview. In this trial, we will assess patient experience of IGR3 compared with IGR2, with a focus on understanding whether the web enhancements led to greater levels of activation and thus greater engagement with managing their health. We will also capture data from health professionals about the experience of implementing web or telephone health coaching in the context of impaired glucose regulation, with a focus on understanding acceptability and feasibility of using web platforms to enhance patient engagement in action planning and behaviour change.

Purposeful maximum variation sampling will be used to identify patient participants sampled for age, baseline body mass index and intervention arm. All interviews will be conducted before outcome analysis is complete, to allow for *a-priori* exploration of user acceptance and experience of implementation. We will aim to conduct approximately 40 interviews in total, comprising approximately 20 participants drawn from both arms of the trial. Where feasible, professionals engaged in the commissioning, management and delivery of the health coaching service will also be interviewed. Up to 15 professional interviews will be conducted.

#### Qualitative data analysis

Interviews will be transcribed verbatim and analyzed thematically using standard approaches informed by Framework [56]. There are five key stages in this type of analysis:Familiarization – the transcripts will be read thoroughly by all researchers to identify key themes.Developing a thematic framework – a framework will be developed that will be applied to the transcripts. Following discussions with co-researchers, this framework will then be expanded and refined.Indexing – themes and emerging sub themes will be labelled and indexed.Charting – framework involves devising a series of thematic charts or matrices.Mapping and interpretation – the aim is to bring out the key characteristics and map and interpret the data as a whole.

A benefit of using Framework analysis is that strategies and recommendations for practice and policy may be elicited at an early stage.

### Data monitoring

The trial will be supervised independently by members of the trial steering committee. This committee will meet twice during the active recruitment period and has responsibility for monitoring progress of the trial, adherence to the protocol, patient safety and consideration of new information. Membership includes the principal investigator ([name]), the chairperson ([name], University of Cambridge, UK), and two other independent members ([name], King’s College London, UK and [name], University of Sheffield, UK). The trial statistician will attend when appropriate. At the chair’s discretion, an observer from Hitachi Europe Ltd will attend the trial steering committee. Given the nature of this trial it is unlikely that there are critical patient safety issues for a separate data monitoring and ethics committee to consider and there will be no formal stopping rules. Terms of reference of the trial steering committee are available on request from the principal investigator.

### Adverse event reporting

An adverse event is any untoward and unexpected medical occurrence in a patient or clinical study subject. Adverse events are likely to be rare but should be reported to the principal investigator by the researcher or Care Call team. Although CATFISH is a trial of a non-investigational medicinal product, serious adverse events that are both related to the research procedures and are unexpected should be reported immediately (within 24 hours) either orally or in writing to the research sponsor (University of Manchester). This immediate report will be followed by a detailed written report sent to the NHS Research Ethics Committee that granted approval for the trial (East of England – Cambridgeshire and Hertfordshire) within 15 days of the study investigator becoming aware of the event.

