**Methods:**

CATFISH is a two-parallel group, single-centre individually randomized controlled trial. Eligible participants are patients aged ≥18 years with impaired glucose regulation (HbA1c concentration between 42 and 47 mmol/mol), have access to a telephone and home internet and have been referred to an existing telephone health coaching service at Salford Royal NHS Foundation Trust, Salford, UK. Participants who give written informed consent will be randomized remotely (via a clinical trials unit) to either the existing pathway (IGR2) or the new web-enhanced pathway (IGR3) for 9 months. The primary outcome measure is patient acceptability at 9 months, determined using the Client Satisfaction Questionnaire. Secondary outcome measures at 9 months are: cost of delivery of IGR2 and IGR3, mental health, quality of life, patient activation, self-management, weight (kg), HbA1c concentration, and body mass index. All outcome measures will be analyzed on an intention-to-treat basis. A qualitative process evaluation will explore the experiences of participants and providers with a focus on understanding usability of interventions, mechanisms of behaviour change, and impact of context on delivery and user acceptability. Qualitative data will be analyzed using Framework.

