### Statistical analysis

We will report the trial and analysis according to CONSORT standards, including full details of use of the various telephone coaching components [43]. The data analyst will be masked to treatment allocation.

For most outcomes, we will present descriptive data on baseline and follow-up scores, to allow assessment of change in IGR2 and IGR3 patients, as well as comparison with outcomes found in pilot evaluations [16, 17]. The focus will be on assessing whether IGR3 achieves at least as good outcomes as IGR2. This will not involve a formal assessment of equivalence.

We will formally test for differences between IGR3 and IGR2 on patient experience using the CSQ-8. Analysis will follow intention-to-treat principles and a pre-specified plan. The core analysis will be via linear regression, using robust standard errors adjusted for the clustering of patients within practices. We will control for baseline values of each outcome and design factors. We will apply multiple imputation to baseline and 9 month variables with missing values by the chained equations approach using scores on all primary and secondary outcome measures (at baseline and follow-up). We will use 20 multiple imputation sets, as this will provide appropriate stability of results. Analyses will be conducted using STATA (version 14) with an alpha significance value of 5 %. We will report standardized effect sizes for all outcomes to aid comparison with published studies.

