### Research ethics

The trial will be conducted in accordance with the UK Department of Health’s Research Governance Framework in health and social care and adhere to the ethical principles of the Helsinki Declaration [57]. All research staff involved in the conduct of the trial will meet the standards laid out in the *ICH Harmonised Tripartite Guideline for Good Clinical Practice* [58]. All participants will be offered a high street voucher worth £20 after completing baseline and the follow-up assessments.

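### The adverse event definition requires events to be unexpected, so foreseeable events fall outside the reporting duty and the later test of unexpectedness is redundant

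*Protocol article*

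**What the plan says.** Three consecutive statements under Adverse event reporting in the protocol article matter here.

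- The definition: "An adverse event is any untoward and unexpected medical occurrence in a patient or clinical study subject".
- The general duty: "Adverse events are likely to be rare but should be reported to the principal investigator by the researcher or Care Call team".
- The expedited duty, to the sponsor within 24 hours, which covers "serious adverse events that are both related to the research procedures and are unexpected". A written report to the ethics committee follows within 15 days.

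Under Data monitoring, the trial steering committee's responsibilities include patient safety. The article holds that "it is unlikely that there are critical patient safety issues for a separate data monitoring and ethics committee to consider", and there are no formal stopping rules.

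Adverse events are not among the outcomes listed in the Abstract or under the outcome headings. The Statistical analysis section names one formal comparison: "We will formally test for differences between IGR3 and IGR2 on patient experience using the CSQ-8".

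**The concern.** Whether an event was expected normally decides how fast, and to whom, a serious event must be reported. Here it also decides whether something is an adverse event at all. The researcher or Care Call staff member would have to judge expectedness before anything is written down, and an event judged foreseeable would leave no record under this section. That applies to serious and related events as much as to minor ones.

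What is at stake is the completeness of the safety record that reaches the principal investigator, in a trial whose safety oversight rests with the steering committee alone. No efficacy result is at stake.

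**Working it through.** The article gives no adverse event rate or expected count, so there is no figure to reproduce. The check is a reading of the rules, followed by an illustration on assumed figures.

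**Step 1: write the rules as sets.** Let U be untoward occurrences, X unexpected ones, S serious ones and R those related to research procedures. Serious adverse events are taken to be a subset of adverse events, since the article gives no separate definition of them.

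| | As written | With expectedness removed from the definition |
|---|---|---|
| Adverse event (report to principal investigator) | U and X | U |
| 24-hour report to sponsor | (U and X) and S and R and X | U and S and R and X |

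**Step 2: compare the rows.**

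- As written, X appears twice in the 24-hour rule. Since X and X is just X, the second mention removes nothing. It has work to do only if some adverse events are expected, which the definition rules out. The definition and the expedited-reporting criterion have been mixed.
- The 24-hour set is the same in both columns: U and S and R and X. Correcting the definition does not change what goes to the sponsor at once.
- The two columns differ only by the events in U that are not in X. These carry no reporting duty as written, even when serious and related.
- The written set lies inside the corrected set. With the same diligence in reporting, the recorded count is therefore equal to or lower than the corrected count, in each arm.

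**Step 3: does a lower count fix the direction of a comparison by arm?** All inputs here are assumptions, expressed as events per 100 participants with at most one event each.

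*Same share dropped in both arms.* Assume true risks of 10 (IGR2) and 15 (IGR3), and a share f that is foreseeable. The recorded difference is (15 − 10)(1 − f), and the recorded ratio is 15(1 − f) / 10(1 − f) = 1.5.

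| f | IGR2 | IGR3 | Difference | Ratio |
|---|---|---|---|---|
| 0% | 10 | 15 | 5.0 | 1.5 |
| 25% | 7.5 | 11.25 | 3.75 | 1.5 |
| 50% | 5 | 7.5 | 2.5 | 1.5 |
| 75% | 2.5 | 3.75 | 1.25 | 1.5 |

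*Different shares by arm, excess hidden.* Assume unexpected events of 5 in each arm, with foreseeable events of 5 (IGR2) and 10 (IGR3). The true difference is (5 + 10) − (5 + 5) = 5. The recorded difference is 5 − 5 = 0.

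*Different shares by arm, excess created.* Assume unexpected events of 4 (IGR2) and 8 (IGR3), with foreseeable events of 8 and 4. The true difference is (8 + 4) − (4 + 8) = 0. The recorded difference is 8 − 4 = 4.

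So the difference can shrink, vanish or be created, and the ratio can stay the same. The definition fixes the direction for counts, but not for contrasts.

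**The case against.** The best defence is that this is loose drafting with little practical effect. The repeated condition in the expedited rule suggests that the authors meant expectedness to act there, and staff may have read the definition in that sense. The article names no event that it regards as expected, so nothing shows what the word would exclude in practice. Both arms receive telephone coaching from the same types of provider, and events are thought likely to be rare. The steering committee's remit also covers patient safety and new information generally, and health and social care use is collected by questionnaire and record linkage regardless of this definition.

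Much of that stands, and it limits the point to a minor one. It does not remove it. The definition is a stated rule, so it is not detail left to a fuller document. Data on service use are not adverse event reports. Rarity may justify light monitoring, but it does not justify a definition that lowers the count.

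A reader might go further and infer that a comparison of harms between arms is understated. The article does not support that: it describes no such comparison, and Step 3 shows that the direction is undetermined.

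Three other arguments are also tempting and should be left out:

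- A list of expected events may sit in the full protocol, so its absence from an article is not a fault.
- That Care Call staff know the allocation, and that IGR3 patients have an additional way to contact an advisor, concern how events come to light. Neither bears on how an event is defined.
- Injury during encouraged activity is a plausible example of a foreseeable event, but the article does not name it.

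**Conclusion.** The point holds as a minor wording fault with a real consequence if followed. As written, foreseeable untoward events are not adverse events and need not reach the principal investigator, and the second test of unexpectedness is redundant. Recorded counts can only be equal to or lower than they would be without that condition.

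The size of the shortfall cannot be estimated from the article. It could be zero if staff ignored the word. Any later comparison by arm could be distorted in either direction or not at all, and the CSQ-8 analysis is untouched.

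The conclusion rests on two assumptions: that the definition is applied as worded, and that the full protocol does not define adverse events differently. If it does, the fault lies in the article's wording alone.

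**What to change.** Delete *and unexpected* from the definition, so that any untoward medical occurrence counts as an adverse event. Keep expectedness only as a criterion for expedited reporting of serious related events, where it already stands.

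The cost is a two-word deletion and a few more event forms to the principal investigator. By Step 2, the 24-hour reports to the sponsor do not change. The Trial status section puts the end of data collection at March 2017 at the latest, so at the time of the article the change could still improve capture during follow-up. Foreseeable events already passed over may not be recoverable, so any account of harms should say which definition was in force when the events were recorded.

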### Research ethics

The trial will be conducted in accordance with the UK Department of Health’s Research Governance Framework in health and social care and adhere to the ethical principles of the Helsinki Declaration [57]. All research staff involved in the conduct of the trial will meet the standards laid out in the *ICH Harmonised Tripartite Guideline for Good Clinical Practice* [58]. All participants will be offered a high street voucher worth £20 after completing baseline and the follow-up assessments.

### Amendments

Substantial amendments will be communicated to the NHS Research Ethics Committee for the East of England (Cambridgeshire and Hertfordshire), following the process outlined by the NHS Health Research Authority. Since starting the trial one substantial amendment has been submitted and granted. This related to permission for a promotional flyer to be used in general practice to promote the Impaired Glucose Regulation Care Call service among general practitioners. This amendment also included provision for the eligibility criteria to be changed to bring the trial into line with evaluation parameters proposed by the NHS National Diabetes Prevention Programme, i.e. only patients with a HbA1c concentration between 42 and 47 mmol/mol in the previous 6 months can be referred into the Care Call service and subsequently invited to take part in the trial.

### Access to data and dissemination policy

As the sponsor of the trial, the University of Manchester will remain the custodians of the data collected from participants during the trial and will not share data with any third party, including private companies, without the consent of the participants. Data will not be released to third parties or private companies (including the funder) before the trial has been completed and will be analyzed by an independent evaluation team at the University of Manchester. No interim analysis is planned and no interim data will be shared with the funder or third parties. In recognition of the importance of transparency and need to increase trust in clinical trial results both Hitachi Europe Ltd, and the University of Manchester will agree to data sharing in accordance with proposals outlined by the International Committee of Medical Journal Editors, which state that authors share with others the deidentified individual-patient data underlying the results presented in the trial report (including tables, figures, and appendices or supplementary material) no later than 6 months after publication [59]. Hitachi, as the funder of the trial and as owners of the technology to be tested, may wish to invoke a brief embargo (up to 3 months) on data sharing before publication in an open-access journal.

## Discussion

Interventions that rely solely on telephone contact (with no self-monitoring of blood glucose) are no more effective than standard care in improving glycaemic control [60], signalling an opportunity to further develop and evaluate interventions that combine telephone interventions with self-monitoring and electronic transfer of data between patients and healthcare providers. Before embarking on expensive and time-consuming trial assessment of clinical effectiveness and cost-effectiveness, however, a key challenge is to understand from the patient perspective if enhancing telephone health coaching interventions with IT platforms improves acceptability and usability and thereby engagement in diabetes prevention programmes. This trial will offer important insights about whether a web-based IT platform can enhance engagement in a telephone health coaching intervention provided by health advisors for people with impaired glucose regulation. The results will have implications for the design of future definitive cost-effectiveness trials in settings where there is no existing diabetes prevention programme.

The trial design is potentially limited by restrictions on participant recruitment. Currently, referral into the Care Call service at Salford Royal NHS Foundation Trust is heavily reliant on general practice and there are limited routes into the service from other sources in the community, e.g. pharmacy and public health. Participants in the CATFISH trial will therefore primarily be drawn from patients already ‘in the system’ and known to general practitioners and may have been given behaviour change advice in the past. Additionally, achieving our recruitment target may be jeopardized by only sourcing participants for the CATFISH trial from referrals into the Care Call service – recruitment into the trial will be contingent on sufficient throughput in the clinical service. However, Salford Royal NHS Foundation Trust is one of seven demonstrator sites for the NHS National Diabetes Prevention Programme in the NHS and there is an ongoing commitment to increase capacity in the Care Call service, with a likely benefit for the CATFISH trial. Furthermore, the Care Call service attracts referrals from all eight neighbourhoods across Salford, increasing opportunities to recruit participants with different socio-economic profiles. The design and recruitment strategy are thus pragmatic and thus more likely to be generalizable.

Working with industry partners in health services research is novel and presents unique challenges, not least the need to maintain independence. Hitachi Europe Ltd, have invested in the Care Call service at Salford Royal NHS Foundation Trust to improve efficiencies, such as employing an administrator and a research nurse to expedite quality referrals into the service. With the support of the trial steering committee, the CATFISH trial is being run as an independent evaluation and we have ensured that sufficient safeguards are in place to preserve independence throughout all phases of the trial. This includes a commitment to open-access publication and data sharing, in keeping with policies to prevent publication and outcome reporting bias of clinical trials.

